## Abstract

**Background::**

Venous thromboembolism (VTE) is one of the leading causes of in-hospital mortality and is responsible for significant healthcare-related costs. However, a clear thromboprophylaxis protocol does not exist in surgery. The conventional method of thromboprophylaxis in surgery includes a combination of chemical and mechanical measures. Studies have shown that the administration of a chemical prophylaxis agent intra-operatively is associated with an increased incidence of surgical bleeding in surgeries such as laparoscopic cholecystectomy (LC). There are two common forms of mechanical prophylaxis: graduated compression stockings (GCSs) and sequential calf compression devices (SCCDs). Recent evidence has suggested several unwanted effects of GCSs, including skin breakage, the development of ulcers, and necrosis. There is a paucity of evidence investigating the use of SCCDs alone intra-operatively in VTE and surgical bleeding prevention.

**Materials and methods::**

This study reports on a multi-center, single-arm, prospective cohort study conducted across 11 hospitals, focusing on LC to standardize the operation. The aim is to recruit 5190 patients, as determined by power calculations, to investigate the incidence of clinical VTE 30 days after surgery. The hospitals involved already have policies in place to use SCCDs alone. All patients undergoing LC will be recruited prospectively, with a 30-day survey conducted to ascertain symptoms of VTE. Any reported symptoms will prompt appropriate radiological confirmation. The secondary outcome of bleeding or other complications arising from VTE prophylaxis will also be collected.

**Results::**

Ethical approval was obtained for this study. Results will be submitted for publication in a peer-reviewed journal and disseminated through participating hospitals.

**Conclusion::**

This study aims to provide information on the incidence of VTE in the LC population following the use of SCCDs only at the time of surgery and to compare it to historical controls of combined SCCDs and GCSs. The benefits include economic, safety, and environmental improvements.

## Introduction

It has been estimated that the Australian annual incidence of VTE is 0.83 per 1000 individuals and is associated with significant morbidity and health-related economic costs. In 2008, the estimated cost to the Australian economy was $1.7 billion[1]. Surgeries with a high risk of VTE include hip or knee replacement, major general, thoracic, vascular, and abdominal laparoscopic surgery^[^2–6^]^. The risk of surgically provoked VTE may be mitigated by the combined use of both chemical and mechanical thromboprophylaxis, as recommended by multiple clinical practice guidelines^[^7,8^]^. When chemical prophylaxis is given at the time of surgery, there is a documented increased risk of bleeding to the point where it is not recommended with certain types of surgery or spinal anesthesia and perhaps should only be given post-operatively in other types of surgery^[^9,10^]^. Despite this, there is no clear recommendation in guidelines regarding the timing of chemical thromboprophylaxis in relation to the operation or the type and duration of mechanical thromboprophylaxis that should be used when chemical prophylaxis is not given.

The exact role of mechanical VTE prophylaxis is not well-researched. The two common modalities used are graduated compression stockings (GCSs) and sequential calf compression devices (SCCDs). GCSs have commonly been used on patients in the ward setting, whereas SCCDs require a dedicated pump for use. In the GAPS study, the use of low molecular weight heparin (LMWH) alone was shown to be non-inferior in terms of the incidence of VTE when compared to the combined use of LMWH with GCSs[11]. This suggests that GCSs added no further protection if chemical prophylaxis is used. However, with the limitations of chemical prophylaxis during surgery, the immediate operative period still relies on mechanical prophylaxis. There is weak evidence suggesting that SCCDs are superior to the use of GCSs as a means of providing mechanical thromboprophylaxis, as evident in the 2012 ACCP guidelines and confirmed in the 2019 ASH clinical practice guidelines^[^7,8^]^. However, although there is no evidence supporting combined use, this is a common practice in operating theaters[12].

There is evidence that the use of GCSs is associated with harm (defined as skin breaks, blisters, ulcers, and necrosis)[8]. This was confirmed in the CLOTS study, with a 5% vs. 1% increase in ulceration and tissue necrosis with GCSs[13]. Additionally, the cost of GCSs is quite significant. The annual cost of the purchase and application of GCSs for surgical patients has been estimated at £63.1 million in England alone[11].

The hypothesis of this study is that SCCDs alone, as mechanical prophylaxis, are non-inferior for VTE prophylaxis when compared to combined mechanical prophylaxis in medium-risk surgery, such as LC. If true, this would eliminate the requirement for GCSs, along with the cost and complication risk, and suggest further studies for high-risk patients.

## Methods and analysis

### Aims and objectives

This study aims to determine if a standardized approach to the intra-operative use of SCCDs only will result in a non-inferior incidence of 30-day symptomatic VTE in patients undergoing either elective or emergency laparoscopic cholecystectomies compared to a reference previously published combined mechanical prophylaxis comparator group from the same mix of centers[12].

There are two main objectives of this prospective point prevalence study:
To determine whether the structured approach of VTE prophylaxis using SCCDs alone is non-inferior with respect to the incidence of symptomatic VTE by day 30 post-operatively when compared to the historical control.To determine the incidence of surgical bleeding and SCCD-related complications.

### Study design

This is a multi-center, prospective point prevalence cohort study of patients undergoing either an emergency or elective laparoscopic cholecystectomy. The incidence of symptomatic VTE at day 30 post-surgical procedure will be compared to a previously obtained incidence of VTE at 0.3%, which was obtained for elective laparoscopic cholecystectomies only, when there was no standardization of timing of chemical thrombo-prophylaxis or the type of mechanical thromboprophylaxis used, although over two-thirds used combined mechanical thromboprophylaxis[12].

The benefits of performing this study as a cohort study are the decreased selection and participation bias, as well as an increased recruitment rate. Utilizing a hospital’s current practice also alleviates the need and cost of widescale pre-operative recruitment and consenting of patients. Given the small number of patients who develop VTE following medium-risk surgery such as LC, the cost and number of patients required for a randomized controlled trial would be impractical, and furthermore, a cohort study provides a more accurate “real-world” result. Given the simplicity of the patient survey in the study and the use of standardized datasets, no patient or public involvement was sought in the development of the protocol.

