### Study population

The study population includes all patients undergoing either an emergency or an elective laparoscopic cholecystectomy. The total number of surgical participants required is 5190, as determined by power calculations. The sample size calculation considered a one-sided proportion test with an assumed rate of VTE of 0.24% in the study population compared to a comparative rate of 0.45%, with an alpha of 0.05 and 0.8 power. The selection of the control rate was guided by the PROTECTinG study[12], with the rate of 0.45% being considered the upper limit of a non-inferiority margin in the rate of VTE. This sample size provides a 95% confidence interval of 0.12% to 0.40% for a point estimate of 0.24% in the observed rate of VTE. This VTE rate of 0.24% represents a 20% reduction in the observed VTE incidence rate reported in the reference study. There is no minimum requirement from each of the various hospital campuses, nor is there any stratification of any of the various hospital campuses.

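### The benchmark is mixed historical practice, so meeting the 0.45% limit would not show that SCCDs alone are non-inferior to combined SCCDs and GCSs

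*Protocol article*

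**What the plan says.** Three places in the protocol article name the comparator as combined mechanical prophylaxis:

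- The Abstract (Conclusion) says the study intends "to compare it to historical controls of combined SCCDs and GCSs".
- The Introduction states the hypothesis that SCCDs alone "are non-inferior for VTE prophylaxis when compared to combined mechanical prophylaxis in medium-risk surgery, such as LC".
- Aims and objectives says the incidence will be "compared to a reference previously published combined mechanical prophylaxis comparator group from the same mix of centers".

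Study design describes the same reference differently. Incidence will be "compared to a previously obtained incidence of VTE at 0.3%, which was obtained for elective laparoscopic cholecystectomies only", at a time when there was no standard for the timing of chemical prophylaxis "or the type of mechanical thromboprophylaxis used, although over two-thirds used combined mechanical thromboprophylaxis".

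Study population then fixes the numbers. The sample size uses a "one-sided proportion test with an assumed rate of VTE of 0.24% in the study population", set against 0.45%, with alpha 0.05 and power 0.8, giving 5190 patients. On the source of the limit it says "The selection of the control rate was guided by the PROTECTinG study", "with the rate of 0.45% being considered the upper limit of a non-inferiority margin in the rate of VTE". It describes 0.24% as 20% below the incidence observed in the reference study. It gives no rate for the reference patients who had combined prophylaxis.

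**The concern.** A single-arm non-inferiority claim can name only the regimen that produced the benchmark. Here the claim names SCCDs plus GCSs, while the benchmark comes from a group in which fewer than a third, but some, had something else. The two descriptions of the control cannot both be right, and the limit is tied to the mixed group.

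The distinction matters because the intended inference is specifically about GCSs. The Introduction says a positive result would remove the need for them, and Setting speaks of confirming that adding them is superfluous. That inference needs a control in which GCSs were added to SCCDs. If the mixed group's VTE rate differs from the rate in its combined-prophylaxis patients, 0.45% represents a different margin against combined prophylaxis from the one the reader is led to see.

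**Working it through.** **Inputs.** From Study design: reference rate 0.3%, and a combined share f above two-thirds. From Study population: limit p0 = 0.45%, assumed rate p1 = 0.24%, one-sided alpha 0.05, power 0.80, N = 5190.

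**1. Reproduce the sample size.** One-sample proportion test, normal approximation:

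n = [(1.645·√(p0(1−p0)) + 0.842·√(p1(1−p1))) / (p0−p1)]²

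= [(1.645 × 0.06693 + 0.842 × 0.04893) / 0.0021]² ≈ 5189

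The stated 5190 reproduces; power at 5190 is 80.0%. The arithmetic is sound. The question is what 0.45% stands for.

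**2. Trace the rates to their source.** 0.24/0.30 = 0.80, which is the 20% reduction the article states. 0.45/0.30 = 1.50. The article does not state a 1.5-fold rule, so that is inferred from the ratio. Both figures scale from the rate of the whole reference group.

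**3. What 0.45% means against combined prophylaxis.** Let pc be the VTE rate in the combined-prophylaxis patients of the reference study, and k the ratio of the other patients' rate to pc. Then

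0.30% = f·pc + (1−f)·k·pc, so pc = 0.30% / (f + (1−f)k)

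and 0.45%/pc = 1.5 × (f + (1−f)k).

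The documents give neither k nor the exact f. Both are assumptions, shown over a range:

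| f | k | pc | 0.45% as a multiple of pc |
|---|---|---|---|
| 2/3 | 0.5 | 0.360% | 1.25 |
| 2/3 | 1 | 0.300% | 1.50 |
| 2/3 | 1.5 | 0.257% | 1.75 |
| 2/3 | 2 | 0.225% | 2.00 |
| 2/3 | 3 | 0.180% | 2.50 |
| 0.85 | 0.5 | 0.324% | 1.39 |
| 0.85 | 1 | 0.300% | 1.50 |
| 0.85 | 3 | 0.231% | 1.95 |

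The multiple is 1.5 only when k = 1. Two-thirds is the lower bound on f, so the first five rows show the widest spread that the article's description allows for each k.

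**4. If the limit were reset from pc.** Apply the inferred 1.5-fold rule to pc and keep N = 5190, a true rate of 0.24% and the test in step 1. At f = 2/3 and k = 0.5, 1, 1.5, 2 and 3, the limit becomes 0.540%, 0.450%, 0.386%, 0.338% and 0.270%. Power becomes 97%, 80%, 52%, 30% and 10%. Resetting the limit is therefore not a neutral edit.

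**The case against.** The strongest defence is that Study design discloses the mixture, most reference patients did have combined prophylaxis, Limitations/risk of bias names the historical control as a limitation, and the first listed objective refers only to the historical control. The disclosure is real, and it makes this a matter of labelling and scope, not concealment. But it does not correct the abstract, the hypothesis or the aim. The limitations mention varying chemical prophylaxis and do not mention the mixed mechanical prophylaxis of the control.

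Four stronger readings are tempting, and the documents do not support them.

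- **That the mixture favours a non-inferiority claim.** The sign is unknown. If the other patients had more VTE than the combined group, 0.45% is looser than it looks; if they had less, it is stricter. Nor is there a separate dilution effect. The study tests one arm against a fixed limit, so the make-up of the reference group acts only through the 0.3%.
- **That the control contained SCCD-only patients because sites overlap.** The article says the same and similar hospitals are included, and that SCCDs alone were adopted before this study. It does not say what the remaining reference patients received.
- **That a specific false-claim rate follows.** With f = 2/3 and k = 2, a true SCCD-alone rate of 1.5 × 0.225% = 0.3375% would pass 33% of the time under an exact one-sided 5% rule (at most 15 events in 5190). It would pass 17% of the time if non-inferiority were read from a two-sided 95% exact interval (at most 13 events). The article states neither rule, and nothing in it supports k = 2.
- **That the closing Conclusion section makes the same error.** It speaks of the conventional method of thromboprophylaxis, which the abstract's Background describes as chemical plus mechanical measures. It does not name combined mechanical prophylaxis as the comparator.

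**Conclusion.** The point holds as a mismatch between the named comparator and the benchmark. The Abstract, Introduction and Aims and objectives promise a comparison with combined SCCDs and GCSs; the 0.3% and the rates built on it come from unstandardised practice that was mostly, not wholly, combined. Meeting 0.45% would support non-inferiority to that mixed practice only.

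Under the stated assumptions (two-thirds combined, k from 0.5 to 3), the limit is 1.25 to 2.5 times the combined-prophylaxis rate; with 85% combined it is 1.39 to 1.95 times. These ranges show how far the meaning of the limit could move in either direction. They are not an estimate of bias. With sign and size unknown, and the mixture disclosed in one section, this should be fixed but does not invalidate the design or its sample size. That the reference group was elective only is a separate matter and is not weighed here.

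**What to change.** 1. In the Abstract (Conclusion), the hypothesis in the Introduction, and Aims and objectives, describe the comparator as mixed, unstandardised historical practice in which most patients had combined mechanical prophylaxis.
2. Limit the non-inferiority conclusion to that comparator. Qualify in the same way the inferences in the Introduction and Setting that GCSs could be dispensed with.
3. Add the mixed mechanical prophylaxis of the control to Limitations/risk of bias.
4. If the numerator and denominator for the reference study's combined-prophylaxis patients can be obtained, report a comparison with that rate as a supporting analysis, and state that it is less precise than the whole-group rate.
5. If the limit itself is reset from that subset, state the rule used to derive it and restate the power at 5190.

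Items 1 to 3 cost only editing and leave the sample size unchanged. Item 4 needs a data extraction from the reference study. Item 5 may be expensive: under the inferred 1.5-fold rule, power at 5190 could fall well below 80%, as the working shows.

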### Setting

This is designed as a multi-center study of surgical patients undergoing a laparoscopic cholecystectomy (either as an elective or an emergency procedure) across eleven hospital campuses in Australia. These hospitals have been selected as they have already adopted the study protocol (SCCDs only) as standard of care and include hospitals similar in demographic to the reference PROTECTinG study[12].

This study will utilize a surgical registrar-run research collaborative to maintain contact with the multiple sites and continue recruitment of registrars who will act as data collectors for the study. This vastly decreases the costs of the study, and if this study confirms that the addition of GCSs is superfluous, this would represent a significant cost benefit as well as environmental savings.

### Study population

The study population includes all patients undergoing either an emergency or an elective laparoscopic cholecystectomy. The total number of surgical participants required is 5190, as determined by power calculations. The sample size calculation considered a one-sided proportion test with an assumed rate of VTE of 0.24% in the study population compared to a comparative rate of 0.45%, with an alpha of 0.05 and 0.8 power. The selection of the control rate was guided by the PROTECTinG study[12], with the rate of 0.45% being considered the upper limit of a non-inferiority margin in the rate of VTE. This sample size provides a 95% confidence interval of 0.12% to 0.40% for a point estimate of 0.24% in the observed rate of VTE. This VTE rate of 0.24% represents a 20% reduction in the observed VTE incidence rate reported in the reference study. There is no minimum requirement from each of the various hospital campuses, nor is there any stratification of any of the various hospital campuses.

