### Primary outcomes

The primary outcome is the incidence of symptomatic VTE by day 30 post-operatively, which is proven by any imaging technique.

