As part of this study, all patients will be contacted between days 30 and 35 post-operatively via telephone to inquire about symptoms that may be suggestive of the development of VTE, irrespective of the clinical follow-up. At this time, verbal consent will be obtained to proceed with a pro forma telephone questionnaire, and this process will occupy approximately 2–5 minutes of their time. For those participants who have symptoms suggestive of a VTE based on the Wells criteria[14], they will be invited back to their treating hospital for image confirmation of VTE, and if this is confirmed, then an anticoagulation regimen will be commenced at the discretion of the clinical team, the duration of which is guided by the latest guidelines from the Thrombosis and Haemostasis Society of Australia and New Zealand[1].

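### The recruitment target of 5190 equals the uninflated calculated sample size, so the stated 80% power holds only if every recruited patient has a known day-30 outcome

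*Protocol article*

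**What the plan says.** Under Study population, the protocol article says "The total number of surgical participants required is 5190, as determined by power calculations". The abstract (Materials and methods) sets the same figure as the recruitment goal: "The aim is to recruit 5190 patients, as determined by power calculations". The number required and the number to recruit are therefore identical.

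The basis is given under Study population: "The sample size calculation considered a one-sided proportion test", with an "assumed rate of VTE of 0.24% in the study population", a limit of 0.45%, and "with an alpha of 0.05 and 0.8 power". The same section gives a 95% confidence interval of 0.12% to 0.40% around 0.24%.

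Under Primary outcomes, the event is symptomatic VTE by day 30 "which is proven by any imaging technique". Under Study method, patients are telephoned between days 30 and 35 and give verbal consent to a questionnaire. If they have suggestive symptoms, "they will be invited back to their treating hospital for image confirmation of VTE". Ethics and dissemination adds an audit of 30-day morbidity and requests for missing data. Safety considerations says that the telephone call is the only item not already collected routinely.

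**The concern.** A sample size from a power formula counts patients who contribute an outcome. A recruitment target normally exceeds it by the expected loss. Here the two are the same number, while the ascertainment route has three steps that can fail: the patient may not be reached, may decline the questionnaire, or may not return for imaging.

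What is at stake depends on how patients with an unknown outcome are handled:

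- **Left out of the analysis.** The evaluable number falls below 5190 and power falls below the stated 80%. The confidence interval widens towards the 0.45% limit.
- **Kept in the denominator as free of VTE.** The observed rate is pulled down. In a single-arm comparison with a fixed limit, this favours a non-inferiority claim.

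Only about 12 events are expected (5190 × 0.0024 = 12.5), so a handful of unknown outcomes can matter.

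**Working it through.** **Inputs (Study population).** Limit p0 = 0.0045; assumed rate p1 = 0.0024; one-sided alpha 0.05 (z = 1.645); power 0.80 (z = 0.842). The abstract describes a "multi-center, single-arm, prospective cohort study conducted across 11 hospitals", so the test is one-sample against a fixed rate.

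**Step 1: reproduce 5190.**

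n = {[z(0.95)·√(p0(1−p0)) + z(0.80)·√(p1(1−p1))] / (p0−p1)}²

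- 1.645 × 0.06693 = 0.11009
- 0.842 × 0.04893 = 0.04118
- n = (0.15127 / 0.0021)² = 5189.0

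This agrees with 5190, so the figure is the bare formula result with no inflation. Other versions do not match: two-sided 6737, continuity-corrected 5656, two-sample one-sided 9639 per arm.

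**Step 2: exact decision rule at 5190.** The protocol does not state a cut-off. The largest count c with P(X ≤ c | n = 5190, 0.45%) ≤ 0.05 is c = 15. This gives type I error 4.5% and power 81.0% at 0.24%.

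**Step 3: unknown outcomes left out.** The documents give no loss rate, so the rates below are assumptions, and loss is taken as unrelated to VTE. Power is at 0.24%. The upper limit is the exact 95% limit at a point estimate of 0.24%, using n × 0.0024 events in every row.

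| Unknown | n | Exact cut-off | Exact power | Normal-approx. power | CI upper limit |
|---|---|---|---|---|---|
| 0% | 5190 | 15 | 81.0% | 80.0% | 0.415% |
| 5% | 4930 | 14 | 78.7% | 77.7% | 0.420% |
| 10% | 4671 | 13 | 76.2% | 75.3% | 0.427% |
| 15% | 4412 | 12 | 73.3% | 72.6% | 0.434% |
| 20% | 4152 | 11 | 70.1% | 69.7% | 0.441% |

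The exact type I error stays below 5% throughout (4.0% to 4.5%). At 2% loss, normal-approximation power is 79.1%. Exact power there is 75.3%, because the cut-off drops by a whole event while n hardly changes.

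The protocol's own upper limit of 0.40% matches an exact interval for 12 whole events (0.120% to 0.404%). The proper baseline for the table is 0.415%, not 0.40%.

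**Step 4: unknown outcomes kept as VTE-free.** With n = 5190 and the rule of 15 or fewer events, if a share m of true VTEs is missed, the chance of passing is P(X ≤ 15 | 5190, p(1−m)).

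| VTEs missed | Pass at true 0.45% (type I error) | Pass at true 0.24% |
|---|---|---|
| 0% | 4.5% | 81.0% |
| 2% | 5.4% | 82.9% |
| 5% | 7.1% | 85.6% |
| 10% | 11.0% | 89.6% |

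Here m is the share of VTEs missed, not the share of calls missed. The two are equal only if no VTE in an unreached patient comes to light by another route.

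**Step 5: recruitment needed to keep 5190 evaluable, 5190/(1−d).** 5464 at 5% loss, 5767 at 10%, 6106 at 15%, 6488 at 20%.

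**The case against.** The strongest reply is that no arithmetic is wrong, that the loss rates are assumed, and that the rules for missing outcomes may sit in the full protocol or an analysis plan not shown. The morbidity audit, the requests for missing data and the routine hospital data could also recover many outcomes without the call. A VTE diagnosed in hospital before day 30 does not need it.

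Much of this stands. The size is conditional, and at low loss it is small. The absence of a missing-data rule in an article is not itself a fault. What does not fall away is that the article itself fixes the recruitment target and attaches a power to it. No later analysis rule can restore patients who were not recruited.

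Stronger readings are tempting but not supported:

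- **That the plan counts unreached, un-imaged and fatal cases as VTE-free.** The outcome definition keeps un-imaged cases out of the numerator and is silent on the denominator. A fatal VTE that was imaged would count.
- **That power and type I error both fail.** They are alternatives. Leaving patients out costs power and does not raise the error rate. Counting missed cases as VTE-free raises the error rate and also raises the chance of passing at 0.24%.
- **That 10% to 20% of calls missed means 10% to 20% of VTEs missed.** The second data source argues against equating them.
- **That the CI limit moves from 0.40% to 0.43–0.44% because of loss.** Part of that gap is a change of method; the like-for-like start is 0.415%.

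**Conclusion.** The point holds in a limited form. The figure of 5190 is correctly calculated, but as a recruitment target it delivers the stated 80% power only with complete ascertainment, which the described follow-up makes unlikely. At an assumed 5% to 20% of outcomes unknown and left out, exact power is about 79% to 70%, and the upper confidence limit moves from 0.415% to 0.42–0.44%. This assumes that loss is unrelated to VTE.

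If unknown outcomes were instead retained as VTE-free, type I error would be about 7% with 5% of VTEs missed and 11% with 10% missed. That is a conditional risk, because the article does not state the handling. The real loss rate and the yield of the morbidity audit are not in the document, so the size cannot be narrowed further. The matter should be corrected because the change is cheap; it does not invalidate the design.

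**What to change.** 1. State that 5190 is the number of patients with an ascertained day-30 outcome and set recruitment above it. Alternatively, keep recruitment at 5190 and restate power and the confidence interval for the expected ascertainment rate.
2. Define the primary denominator as patients with a completed call or an outcome known from the hospital record or the morbidity audit.
3. Report a supportive tipping-point analysis covering unreached patients, symptomatic patients without imaging, and deaths without imaging. Leave the imaging-proven primary endpoint unchanged. Adding death-certificate diagnoses to it, or requiring the claim to survive counting every symptomatic un-imaged patient as an event, would be debatable changes and is not needed here.

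Cost: restating is a wording change with slightly less favourable stated power, plus a little extra analysis. Keeping 5190 evaluable means more recruitment, for example 5464 at 5% loss or 5767 at 10%.
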